## 1. Introduction

National and international Diabetes Associations endorse physical activity and regular exercise in people with type 1 diabetes (T1D) [1]. Exercise improves weight management, cardiovascular fitness, insulin sensitivity and wellbeing [2]. However, studies did not reveal a significant improvement in glycaemic control as measured by HbA1c when patients were exercising regularly [3]. A reason for this finding might be the mismatch of insulin dose reduction and carbohydrate intake. Standard recommendations around exercise suggest pre-exercise bolus insulin reductions or even basal insulin dose reductions when patients are exercising more regularly [4][5][6]. Especially, early (>2 hrs) and excessive pre-exercise bolus insulin dose reductions may mask the beneficial effects of exercise on glycaemic control.

Little research exists on therapy strategies around high intensity exercises [4] or sports competitions in individuals with T1D [7]. During high-intensity exercise several physiological mechanisms underpin the complexity of therapy management in individuals with T1D: use of muscle glycogen and blood glucose as preferred fuel with minimal contributions from lipid and protein [8], increased concentrations of counterregulatory hormones like adrenaline, noradrenaline and cortisol [9] which might increase blood glucose concentration during exercise, increased risk of post-exercise hypoglycaemia due to higher absolute work rates and hepatic glycogen depletion etc. Precise strategies around prolonged high-intensity exercise are currently missing and might hinder people with T1D to compete in sports.

Therefore, the aim of this prospective study is:

- to investigate the effects of a running competition preparatory training on glycaemic control (HbA1c, fructosamine, time spent in glycaemic ranges) in individuals with T1D
- to explore the changes in cardio-pulmonary markers following a running competition preparatory training and explore links to resultant running performance in individuals with T1D
- to characterise exogenous insulin and carbohydrate administration strategies that aim to increase the time spent in euglycemia during running competition
- to characterise the glycaemic variability in response to running a competition
- to characterise the physiological demands of running a marathon in people with T1D

## **2. Research Question**

This prospective controlled study aims to investigate the effects of regular physical exercise in preparation for a road running competition on glycaemic control, time spent in glycaemic ranges and cardio-pulmonary markers

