## **3. Methods and Material**

### **3.1. Investigation Plan**

The study will be performed in a prospective, non-interventional, observation design over a period of 10-12 weeks, consisting of 3 cardio-pulmonary exercise (CPX) tests, 3 venous HbA1c and fructosamine measurements and a road running competition.

The Outpatient Clinics for Diabetes at the Medical University of Graz has accompanied and supported subjects with type 1 diabetes running at the Graz marathon over the last years already. This year subjects already planning to participate will participate in a structured and prospective observation study to record insulin treatment changes during the preparation phase, the marathon and the weeks thereafter.

After assessment of eligibility criteria, a comprehensive sports medical examination will be performed ahead of study inclusion to minimise the risk of exercise-induced adverse events. Participants will receive a written general training recommendation in preparation for the competition depending on individual capacities and aims. Additionally, detailed therapy strategies around exercise (insulin dose reductions, exercise carbohydrates, glycogen filling, hydration etc.) will be given to the participants. On the day of screening, patients will be fitted with a flash glucose monitoring system (if not already used) and insulin dosings, carbohydrates, exercise etc. will be documented digitally on the flash glucose monitoring system. Specific details on performed exercises (type, intensity, mode, duration) will be documented in an additional diary. Patients will receive a heart rate monitor which needs to be worn during the exercise sessions and at the day of competition (Fig1):

[figure not shown]

Figure 1: Study flow chart. FGM = flash glucose monitoring, CPX = cardio-pulmonary exercise test.

Over all, the study consists of 3 visits and a competition (the training group does not participate in the competition because of the study but participate in the study because they participate in the competition). The first visit includes the assessment of eligibility, written informed consent procedure, a medical examination, FGM fitting and the first CPX testing. At the second and third visit, participants will perform again a cardio-pulmonary exercise (CPX) test on the track to determine the first (VT1) and second ventilatory threshold (VT2) as well as the heart rate turn point (H RTP) [10][11].

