#### 3.2.1. Inclusion Criteria

- 1) Type 1 Diabetes
- 2) Aged: 18 – 65 years (both inclusive)
- 3) A1c 5.5% - 10% (37 – 113 mmol.mol) (both inclusive)
- 4) Multiple daily insulin injections (MDI) or insulin pump therapy (CSII)
- 5) Diabetes diagnosed > 12 months
- 6) BMI 18.5 – 30 kg/m^2 (both inclusive)
- 7) Planned participation at the Graz marathon

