### 3.6. Primary Endpoint

- Difference in HbA1c and Fructosamine from screening visit to last visit

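### Section 2 calls this a controlled study of exercise effects, but nothing controls the HbA1c and fructosamine endpoint, so its before-after change cannot be credited to training alone

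*Protocol*

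**What the plan says.** The protocol describes its design in two ways. Section 2 says "This prospective controlled study aims to investigate the effects of regular physical exercise". Section 3.1 says "The study will be performed in a prospective, non-interventional, observation design over a period of 10-12 weeks". The first aim in section 1 is likewise causal: "to investigate the effects of a running competition preparatory training on glycaemic control".

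The primary endpoint (section 3.6) is the difference in HbA1c and fructosamine "from screening visit to last visit". One inclusion criterion for participants with diabetes (section 3.2.1) is "Planned participation at the Graz marathon". The only other people in the study are the 10 healthy volunteers of section 3.2.3, who receive a glucose sensor and an ECG before the race and have both removed after it.

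Participants with diabetes also receive several things from the study:

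- Section 3.1 on the day of screening: "patients will be fitted with a flash glucose monitoring system (if not already used".
- Section 3.1, without a date: "detailed therapy strategies around exercise (insulin dose reductions, exercise carbohydrates, glycogen filling, hydration etc.) will be given to the participants", together with a written training recommendation.
- Section 3.4: a daily carbohydrate target for the preparation period, advice on insulin doses, and a discussion of insulin therapy and training at each CPX visit, with individual adjustment where needed. This section calls the period an intervention.

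**The concern.** A controlled study of an effect needs a comparison that shows what would have happened to the same outcome without the exposure. If the primary endpoint has no such comparison, the word *controlled* claims a property that the design lacks, and the question about the effects of exercise cannot be answered by the endpoint chosen for it.

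What is at stake is the main conclusion. A report that followed section 2 would present a fall or rise in HbA1c as the effect of training, shown in a controlled study. The same change could come partly or wholly from starting a sensor, or from the insulin and carbohydrate advice that the study itself provides.

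**Working it through.** The protocol states no figure that bears on this point. Section 5 sets 6-10 participants by availability, with no effect size, standard deviation or power. The check therefore sets the sections side by side.

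**1. Is there a control for the primary endpoint?**

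| Possible control | What the protocol says | Can it control HbA1c or fructosamine? |
|---|---|---|
| People with diabetes who do not train | Planned marathon participation is an inclusion criterion (3.2.1); section 5 draws the sample from the runners | No such group is described |
| Healthy volunteers | Sensor and ECG placed before the race, removed after it (3.2.3); no HbA1c or fructosamine listed | No, on the text shown |
| A term in the endpoint itself | Within-person difference, screening to last visit (3.6) | No between-group comparison |

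None of the three supplies a control. The flow chart (Figure 1) is not shown, but a further arm in it would conflict with the population and sample-size text.

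**2. What else changes between screening and last visit?**

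| Component | Timing stated | Who |
|---|---|---|
| Flash glucose monitoring | Day of screening (3.1) | Those not already using it; number not given |
| Therapy strategies | Not dated (3.1) | Participants generally |
| Carbohydrate target | For the preparation period (3.4) | Participants generally |
| Insulin-dose advice | During what section 3.4 calls the intervention | Participants generally |
| Review of insulin therapy and training | Each CPX visit (3.4) | Participants generally, individualised where needed |

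Visit 1 also provides the baseline HbA1c and fructosamine, so for new users the sensor starts at baseline. The other components come at entry or during preparation, with no exact start given. All fall within the interval over which the primary endpoint is measured.

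**3. Could these components plausibly move the endpoint?** On the protocol's own reasoning, yes. Section 1 suggests that earlier studies may have found no HbA1c benefit from regular exercise because insulin reduction and carbohydrate intake were mismatched. It thus treats the handling of insulin and carbohydrate as a driver of HbA1c, and the study then advises on exactly that handling.

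**4. Can the parts be separated?** Write the expected change as

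change = training + sensor (new users) + advice and review + anything else over the period.

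A single before-after difference estimates only the sum. In participants who already used a sensor the second term drops out, but advice and review remain. This holds at any sample size.

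**5. Could the analysis plan supply the answer?** The statistical analysis plan is not at hand. Section 4 says that it will be finished before database lock. It can choose summaries or models, but it cannot create a comparator that was not enrolled or measured.

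**The case against.** The strongest reply is that the fault is mainly one word in an otherwise modest plan. Section 3.1 gives the operative design as observational, most of the other aims are to explore or characterise, section 4 names only descriptive statistics, and section 5 claims no hypothesis or power. A descriptive before-after study of 6-10 runners is legitimate. All of this stands, and it is why the remedy is wording and not a new arm. It does not remove the point: the wrong word sits in the research question, and the causal wording is in sections 1 and 2.

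Four stronger readings are tempting, and the documents do not support them.

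- A reader might infer that all the co-interventions start on the day of baseline. Only the sensor is dated to screening. Section 3.1 also says that the clinic has supported marathon runners with type 1 diabetes in past years, so such support may not be new to everyone.
- A reader might add regression to the mean. Entry requires HbA1c between 5.5% and 10%, bounded at both ends, together with planned race participation. Nothing selects for extreme baseline values.
- A reader might put a number on the non-training share, or point to wide confidence intervals at this sample size. The share of new sensor users, the effect of a sensor and the spread of change are all absent from the documents. The problem is also confounding, not precision.
- A reader might take the sentence beginning "the training group does not participate in the competition because of the study" to imply a missing untrained arm. The term can simply distinguish the runners with diabetes from the healthy volunteers, so it need not be removed.

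That the volunteers have no HbA1c or fructosamine measurement is inferred from section 3.2.3, which lists neither. It is not stated outright.

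**Conclusion.** The point holds and the text is wrong as written. The protocol claims a control that it does not define for HbA1c or fructosamine, and it words an uncontrolled change as an effect of exercise. That change also contains sensor initiation in new users and the therapy, carbohydrate and insulin support given by the study.

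Its size cannot be stated from the documents. The non-training part could be anything from nil to the whole observed change, and enrolling more runners would not narrow it.

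The conclusion rests on two readings: that section 3.2.3 lists everything planned for the volunteers, and that the missing flow chart adds no arm. It needs no assumption about the sensor's effect, because the advice and review alone are enough to prevent attribution to training.

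**What to change.** - **Section 2:** delete *controlled*.
- **Sections 1 and 2:** restate the aim as describing the change in HbA1c and fructosamine, from screening to last visit, in runners with type 1 diabetes who prepare for a race with study-provided monitoring and advice.
- **Same place:** state that this change is not attributable to exercise alone.
- **Section 3.2.3:** describe the healthy volunteers as a race-day comparison only.
- **Sections 3.1 and 3.4:** reconcile the *non-interventional* label with the reference to an intervention. What participants are advised is not at issue here; the two descriptions must agree.

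Optional and cheap: record flash-monitoring use before screening as one baseline item, and list individual changes by prior use. This would be descriptive only, since 6-10 people split in two leaves a handful in each part, and the advice remains mixed with training in both.

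The cost is protocol wording, with no new arm, visit or measurement. The price is a weaker claim, which is the one the design can support.

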## **3. Methods and Material**

### **3.1. Investigation Plan**

The study will be performed in a prospective, non-interventional, observation design over a period of 10-12 weeks, consisting of 3 cardio-pulmonary exercise (CPX) tests, 3 venous HbA1c and fructosamine measurements and a road running competition.

The Outpatient Clinics for Diabetes at the Medical University of Graz has accompanied and supported subjects with type 1 diabetes running at the Graz marathon over the last years already. This year subjects already planning to participate will participate in a structured and prospective observation study to record insulin treatment changes during the preparation phase, the marathon and the weeks thereafter.

After assessment of eligibility criteria, a comprehensive sports medical examination will be performed ahead of study inclusion to minimise the risk of exercise-induced adverse events. Participants will receive a written general training recommendation in preparation for the competition depending on individual capacities and aims. Additionally, detailed therapy strategies around exercise (insulin dose reductions, exercise carbohydrates, glycogen filling, hydration etc.) will be given to the participants. On the day of screening, patients will be fitted with a flash glucose monitoring system (if not already used) and insulin dosings, carbohydrates, exercise etc. will be documented digitally on the flash glucose monitoring system. Specific details on performed exercises (type, intensity, mode, duration) will be documented in an additional diary. Patients will receive a heart rate monitor which needs to be worn during the exercise sessions and at the day of competition (Fig1):

[figure not shown]

Figure 1: Study flow chart. FGM = flash glucose monitoring, CPX = cardio-pulmonary exercise test.

Over all, the study consists of 3 visits and a competition (the training group does not participate in the competition because of the study but participate in the study because they participate in the competition). The first visit includes the assessment of eligibility, written informed consent procedure, a medical examination, FGM fitting and the first CPX testing. At the second and third visit, participants will perform again a cardio-pulmonary exercise (CPX) test on the track to determine the first (VT1) and second ventilatory threshold (VT2) as well as the heart rate turn point (H RTP) [10][11].

Afterwards patients will be exercising regularly in preparation for the competition and document insulin therapy, carbohydrate intake and exercise frequency on their FGM as well as specific details around exercise in a diary. CPX tests will be repeated as given in figure 1. At the screening visit and CPX visits HbA1c and fructosamine will be measured obtained from venous blood.

#### Visit plan:

1. Visit: Screening, informed consent, insertion of flash glucose monitoring (FGM) sensor, CPX test, measure of HbA1c and fructosamine
2. Visit: CPX test, measure of HbA1c and fructosamine

#### Running competition

3. Visit: CPX test, measure of HbA1c and fructosamine

The exercise tests will be performed at the University of Graz (AUT). The Medical University of Graz (AUT) will recruit the participants and will also perform the medical examination. Diabetes specific markers will be analysed at the laboratory of the Medical University of Graz and at the sport science laboratory of the University of Graz (AUT).

### 3.2. Study population

Study participation is voluntarily after enlightenment by the study physician and given signed informed consent.

#### 3.2.1. Inclusion Criteria

- 1) Type 1 Diabetes
- 2) Aged: 18 – 65 years (both inclusive)
- 3) A1c 5.5% - 10% (37 – 113 mmol.mol) (both inclusive)
- 4) Multiple daily insulin injections (MDI) or insulin pump therapy (CSII)
- 5) Diabetes diagnosed > 12 months
- 6) BMI 18.5 – 30 kg/m^2 (both inclusive)
- 7) Planned participation at the Graz marathon

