#### **5. Sample Size**

As we will collect data on subjects with type 1 diabetes participating in the Graz marathon competition and do not proactively recruit subjects for this non-interventional study, we will include approximately 6-10 subjects, depending on the number of people taking part in the marathon competition this year.

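### The upper HbA1c limit for inclusion is printed as 10% and as 113 mmol/mol, which are not the same value, so eligibility between about 86 and 113 mmol/mol cannot be decided

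*Protocol*

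**What the plan says.** Protocol section 3.2.1, criterion 3, gives one HbA1c range in percent and repeats it in brackets in mmol/mol: "A1c 5.5% - 10% (37 – 113 mmol.mol". The limits are marked "both inclusive".

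No other section of the protocol text at hand restates the limit or says which unit governs. The exclusion criteria (3.2.2) contain no HbA1c limit. Section 3.1 has diabetes markers analysed at two laboratories, and section 3.5.2 describes sampling and assay, but neither fixes a reporting unit.

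HbA1c is also an outcome. Section 3.6 defines the primary endpoint as the difference in HbA1c "and Fructosamine from screening visit to last visit", so the screening value serves as both eligibility value and baseline. On size, section 5 states that "we will include approximately 6-10 subjects" with type 1 diabetes. Section 4 foresees descriptive statistics in an intention-to-treat and a per-protocol dataset.

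**The concern.** A bracketed second range normally means the same range in another unit. Here the lower ends match and the upper ends do not, so the criterion contains two different upper limits. Two screeners who each apply the text correctly, one in percent and one in mmol/mol, can reach opposite decisions on the same blood sample.

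Two things are at stake. First, entry to the study, and with it the maximal cardio-pulmonary tests, cannot be settled for anyone in the disputed band. Second, if such a person is enrolled, the text does not say whether this is an eligibility deviation, which a per-protocol dataset may need to know. A further, conditional matter is that the variable concerned is a component of the primary endpoint in a very small group.

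**Working it through.** **Inputs from the protocol.** Percent limits 5.5 and 10; mmol/mol limits 37 and 113 (both section 3.2.1); n about 6 to 10 (section 5).

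**Assumption.** The conversion equation is not printed in the protocol. The standard one is used as a fixed unit conversion: NGSP (%) = 0.09148 × IFCC (mmol/mol) + 2.152, so IFCC = (NGSP − 2.152) / 0.09148. The protocol's own lower pair serves as the check on it.

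**Step 1: reproduce the lower limit.** (5.5 − 2.152) / 0.09148 = 36.6, printed as 37. It agrees.

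**Step 2: try the upper limit.** (10 − 2.152) / 0.09148 = 85.8, about 86. The protocol prints 113. It does not agree.

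**Step 3: reverse the upper limit.** 0.09148 × 113 + 2.152 = 12.49%, about 12.5%. The protocol prints 10%.

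**Step 4: robustness.** Two other common forms, IFCC = 10.93 × NGSP − 23.5 and IFCC = (NGSP − 2.15) × 10.929, give 85.80 and 85.79 for 10%. The choice of form does not matter.

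**Step 5: slope.** The printed pairs imply (113 − 37) / (10 − 5.5) = 76 / 4.5 = 16.9 mmol/mol per percentage point. The conversion has 1 / 0.09148 = 10.93. No single linear conversion with that slope fits both printed pairs.

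**Step 6: the disputed band.** 86 mmol/mol converts back to 10.02%, which is 10.0% to one decimal, so it meets both limits. Above that and up to 113 mmol/mol (above 10% and up to about 12.5%), the percent limit excludes and the mmol/mol limit admits. The width is 113 − 86 = 27 mmol/mol, or 12.5 − 10 = 2.5 points.

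**Step 7: largest shift in the baseline mean.** If one participant enters at exactly 113 in place of one at exactly 86, the mean at screening moves by 27 / n:

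| n | mmol/mol | percentage points |
|---|---|---|
| 10 | 27 / 10 = 2.7 | 2.5 / 10 = 0.25 |
| 6 | 27 / 6 = 4.5 | 2.5 / 6 = 0.42 |

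**Step 8: the endpoint itself.** The mean change is the sum of (last − screening) divided by n. Swapping one participant for another moves it by (difference between their two changes) / n. The starting level does not enter by itself. Each 1 mmol/mol by which their changes differ moves the mean change by 1/10 = 0.10 to 1/6 = 0.17 mmol/mol. The protocol gives nothing from which to set that difference.

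**The case against.** The best defence is that this is a slip in a bracket. The percentage comes first, so a natural reading treats it as the limit and the mmol/mol figure as a faulty conversion. That is plausible, but the protocol does not say so, and the reverse cannot be ruled out. A digit misread from the PDF cannot be fully excluded either, though the rest of the line is intact and nothing suggests one.

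A second defence is practical. This is a small, non-interventional study of people already planning to run, analysed descriptively. Nothing shows that anyone lies in the band, and if nobody does, neither enrolment nor results change. This stands, and it limits the severity.

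Three stronger readings are tempting, and the documents do not support them:

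- *That the limit decides who runs the race.* Section 3.1 says that runners join the study because they are competing, not the other way round, and criterion 7 requires that participation is already planned. The limit governs study entry and the exercise tests only. Even there it is not the sole gate: section 3.1 requires a sports medical examination before inclusion, and section 3.2.2 has an investigator-judged exclusion for illness. Neither resolves the mismatch.
- *That one high entrant would drive the mean change.* The figures in step 7 concern the baseline mean. A high starting value is present at both visits and cancels unless that person changes more than the others.
- *That the mismatch builds in regression to the mean.* A looser upper cap does not select for high screening values; it only trims less of the upper tail. One extreme person may regress, but the ambiguity does not by itself bias the group mean.

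Nor can one say that admission turns on the unit a laboratory reports, because the protocol does not state the reporting unit.

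**Conclusion.** The point holds as an internal contradiction in an eligibility threshold. The two printed upper limits differ by about 27 mmol/mol (2.5 percentage points), and a person above about 86 and up to 113 mmol/mol is excluded by one and admitted by the other. Study entry and eligibility-deviation status for that person cannot be determined from the protocol.

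The conclusion rests on one assumption, the standard unit conversion, which the protocol's lower pair bears out. Which limit was intended cannot be settled from the text.

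The effect on results is conditional on someone falling in the band. If so, the baseline mean could move by at most 2.7 (n = 10) to 4.5 mmol/mol (n = 6) per person; the effect on the mean change is not determined. Severity: should be fixed. It is more than clerical because it is a decision threshold, but no harm to the primary result has been shown.

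**What to change.** The sponsor should decide which upper limit is meant and print one pair that agrees in both units. As arithmetic only, 10% pairs with 86 mmol/mol and 113 mmol/mol pairs with 12.5%; the choice between them is the sponsor's. Stating which unit governs would remove any doubt from rounding at the boundary.

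Any participant already screened with HbA1c above about 86 and up to 113 mmol/mol should then be checked against the reconciled limit, and the eligibility decision documented.

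Cost: a one-line amendment to section 3.2.1 and a review of at most a handful of screening records. No extra data are needed.
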